### 7.1. Definitions for adverse events

There is currently no clear definition of adverse events during training with oncological patients. The term "adverse events", originally established in medicine, is used to record and analyse adverse events during drug trials. In the field of oncological exercise therapy, the definition of adverse events is different than in drug trials. To classify different degrees of severity, serious adverse events (SAEs) and non-serious adverse events (AEs) are defined as follows:

#### 7.1.1. Adverse event (AE)

„These are health incidents that lead to a short-term impairment of physical functioning or health and are at most clarified by a doctor, but do not require treatment" [21].

The AE does not necessarily have to be causally related to the training. All events that occur during training (including performance diagnostics) are recorded as AEs.

AEs include, for example, dizziness, nausea or vomiting occurring during training or performance diagnostics. They also include sprains, ligament strains, torn muscle fibres and the like caused by training.

#### 7.1.2. Serious adverse event (SAE)

"These are health incidents during training that result in a medium or long-term impairment of physical functioning or health and result in medical treatment (death, cardiac arrest requiring resuscitation, broken bones, incisional fractures and injuries)." [21]

SAEs during the performance of the study are incidents that are

- a) are fatal or life-threatening,
- b) require unscheduled hospitalisation and/or

c) require medium-term health impairment with medical treatment (e.g. conventionally treated bone fracture)

The SAE does not necessarily have to be causally related to the training. Events are considered life-threatening in the above context if there was a risk of death at the time of the event.

Any inpatient stay of a study participant that lasted at least one night (10 pm - 6 am) is considered a hospitalisation.

## **7.2. Documentation and tracking of AEs/SAEs**

During the 12-week training intervention, which takes place in a home-based setting, all study participants are called once a week by their local therapist. The therapist asks about any adverse events (AEs and SAEs) that occurred during the training programme and documents these in a "telephone log" (Appendix 8). It should also be recorded during which the event occurred (endurance training, strength training, balance training, etc.).

After completion of the training intervention, the protocols are sent to the study management/study centre of the UMR, where all documented AEs/SAEs are collated.

During the follow-up period (12-week follow-up), the study participants inform their therapist of any incidents that occurred during training. In such cases, the therapist notifies the study centre of Clinic III, Haematology, Oncology and Palliative Medicine at UMR by fax or e-mail after being informed.

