#### **4.5. Intervention**

The training intervention takes place in a home-based setting over a period of 12 weeks. Patients are recommended to do the individually tailored exercises at least three days a week. The training duration per day should be 15 - 30 minutes. The patient is also recommended (in addition to training the exercises) to do endurance training 2 to 3 times a week for around 30 minutes, e.g. in the form of a walk, (Nordic) walking, cycling, swimming, dancing or similar. In order to avoid overloading through training, the BORG scale (see Appendix 6) is recommended for controlling the training. The Borg scale from 6 ("very, very easy") to 20 ("very, very strenuous") measures the individually perceived level of exertion during strength and endurance training. The optimum effort lies between the values 11 and 15.

The individual exercise programme is put together by sports scientists and/or physiotherapists based on the results of the initial diagnostics. Various mobilisation, coordination, strengthening and stretching exercises are used according to the patient's performance capacity/restrictions, which are believed to have positive effects on physical performance, functionality and QoL. All recommended exercises can be found in the "Exercise manual for patients with mouth, jaw, face and neck tumours", which the study participants receive. In addition, the selected exercises are saved as a video on a data carrier (DVD/stick), which the patient also receives. Depending on the feedback from the participants, it is possible to recommend further exercises after the first training sessions and make them available as video files (e.g. more demanding or more difficult exercises to improve performance). Materials such as elastic bands and exercise balls, which are required for the exercises, are provided to the patient free of charge.

The patient records their training in a training diary. Once a week, a local therapist calls the patient to enquire about the status quo and records this.

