## 7. Safety

To date, there is little data available on the occurrence of adverse events (AEs) in the routine care of oncological patients. To date, the occurrence of AEs in the training of oncological patients has mainly been recorded in the context of clinical studies. Based on previous results, training with oncological patients is considered to be feasible and safe [19,20], as the probability of an "adverse event" occurring can be considered low [21].

No medication is administered as part of this study. All examinations as part of the performance diagnostics are non-invasive. The training takes place in a home-based setting. The recommended exercises are adapted to the individual patient's state of health and current performance capacity. The training times, training volume and training intensity are determined independently by the study participants. It is expressly pointed out that training should not be carried out in the event of nausea/vomiting, severe pain, impaired consciousness and confusion, dizziness, circulatory problems, fever > 38° or severe infection. Nevertheless, incidents (e.g. nausea/vomiting, muscular complaints, circulatory problems) cannot be ruled out due to the unaccustomed strain.

In order to record any incidents that may occur, the patients are called once a week by the local therapist during the home-based intervention and the status quo is enquired about and incidents that were supposedly related to the home-based training are documented. A distinction is made between AEs and SAEs.

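### For SAEs in the 12 training weeks the protocol states no notice to the study centre before training ends, and section 7 conflicts on which events count

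*Protocol*

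**What the plan says.** **Reporting during the intervention.** Section 4.5 sets the length: "The training intervention takes place in a home-based setting over a period of 12 weeks". Under section 7.2 the local therapist phones each participant weekly, asks about AEs and SAEs and writes them in a telephone log. The route to the centre is then: "After completion of the training intervention, the protocols are sent to the study management/study centre of the UMR, where all documented AEs/SAEs are collated". Section 7.2 gives no separate SAE route and no time limit for this period.

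**Reporting during follow-up.** In the next paragraph of section 7.2, participants tell their therapist about incidents, and "In such cases, the therapist notifies the study centre" by fax or e-mail after being told.

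**What is recorded.** The opening of section 7 says that "incidents that were supposedly related to the home-based training are documented". Section 7.1.1 says: "The AE does not necessarily have to be causally related to the training". It adds that every event occurring in training, performance diagnostics included, is recorded as an AE. Section 7.1.2 repeats the no-causality rule for SAEs.

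**Definitions.** The AE definition, quoted in 7.1.1 from a cited source, covers short-term impairments that "are at most clarified by a doctor, but do not require treatment". The SAE definition quoted in 7.1.2 covers incidents in training that "result in a medium or long-term impairment of physical functioning or health and result in medical treatment". The protocol's own list below it covers incidents while the study is being carried out: fatal or life-threatening events, unscheduled hospitalisation, or medium-term impairment with medical treatment.

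**The concern.** The study centre compiles each patient's training plan and exercise programme (section 4.1), and further or harder exercises may be added after training has begun (section 4.5). It therefore has a use for serious-event information while training is under way. Yet the stated route in those weeks is slower than the one for the follow-up period.

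The second issue is what a count of events would mean. If one passage restricts documentation to presumed training-related incidents and two others do not require relatedness, sites in a multicentre study can follow the same protocol and record different things. Adverse events are among the intervention data to be collected and described (Synopsis, Data analysis; section 4.6.1), so the description would mix recording practices.

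**Working it through.** The protocol gives no figure for reporting time, so there is nothing to reproduce. The check is a comparison of passages plus simple arithmetic.

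**Inputs.** Intervention 12 weeks (4.5). Calls once a week (7.2). N = 60 (Synopsis; 6.2). Recruitment 12 months (4.1, study schedule).

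**Step 1: delay under the text as written.** Take completion to mean completion by the individual patient, which is the favourable reading; section 7.2 does not say. An event in week k is known to the site by that week's call, and the log leaves at the end of week 12 at the earliest:

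lag = 12 − k weeks, plus an unspecified sending time.

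- k = 1: 12 − 1 = 11 weeks
- k = 6: 12 − 6 = 6 weeks
- k = 12: 0 weeks

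If events were spread evenly over the weeks (an assumption), the mean lag from the call is (11 + 10 + … + 0)/12 = 66/12 = 5.5 weeks. In follow-up the notice is triggered by the event, so no such lag is built in, though no time limit is given there either.

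**Step 2: how many patients start meanwhile.** Assuming even recruitment, 60 patients / 52.18 weeks = 1.15 per week, and 1.15 × 12 = 13.8. About 14 further patients would be included during one patient's 12 weeks.

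**Step 3: recording rules side by side.**

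- Section 7, opening: incidents presumed related to the home training.
- 7.1.1: all events in training or performance diagnostics, causal link not needed.
- 7.1.2, quoted definition: incidents in training.
- 7.1.2, the protocol's own list: incidents while the study is being carried out, causal link not needed.
- 7.2: the therapist asks about events that occurred in the training programme.

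Take an unscheduled hospitalisation in week 5, unrelated to training and not arising in a session. Under the list in 7.1.2 it is an SAE. Under the definition quoted just above that list it is not. Under the opening of section 7 it is not documented. Under 7.2 it depends on whether the training programme means the sessions or the 12 weeks.

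**Step 4: the boundary between AE and SAE.** Take a short-term event in training that is treated without admission and is not life-threatening. It fails the quoted AE definition because it was treated, and fails the SAE definition because the impairment is not medium-term. However, 7.1.1 also records all events in training as AEs, so it is captured. The conflict is between two statements within 7.1.1.

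**The case against.** **The centre can be reached at any time.** Section 4.1 provides for contact between sites and study management by e-mail, telephone or video conference throughout the study. Section 7.2 says where logs go for collation; it does not tell sites to hold SAEs back. A reader might infer that serious events are withheld and that the centre cannot react. The text does not support that: a site may well call. But that contact is on an if-needed basis, with questions as its example, and is not a reporting duty. What stands is that no duty to notify is stated for these weeks.

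**The period is not shown to be the riskiest.** A reader might describe the 12 weeks as supervised and of highest risk. Training is home-based and self-directed with a weekly call; the supervised study was the earlier pilot (2.2). No section ranks risk by period. The comparison of routes does not need either claim.

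**Section 7.2 has no relatedness test.** The condition stands in the introduction to section 7, in the passive, and nothing says that the therapist applies it as a filter. The telephone log (Appendix 8) is not at hand and may already hold a relatedness field. This softens the conflict but leaves two incompatible statements in force.

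**Treated minor events are not shown to be lost.** A reader might conclude that short-term treated events fall between the classes and lower the count. The all-events rule in 7.1.1 answers that for events in training. Nor does the protocol say that its AE examples, such as strains and torn muscle fibres, need treatment.

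**Plans are individual.** One patient's SAE need not bear on the next 14. This is fair, and that number is only an illustration.

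**Conclusion.** The point holds in two main parts and one minor one. First, no SAE notification duty is stated for the 12 weeks, and the only stated route can delay the information by up to about 11 weeks after the site knows, plus sending time. This rests on completion being per patient and on logs going at week 12; the protocol does not say when the logs of a patient who stops early are sent, so the delay may be shorter for such patients. Second, the rules on relatedness and on the SAE window contradict each other, so counts can vary by site. Third, and minor, the quoted AE definition conflicts with the all-events rule beside it.

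The number or share of events affected cannot be derived from the protocol, so a definite downward bias in the count is not established. The figure of about 14 inclusions depends on even recruitment. Safety is neither a primary nor a secondary outcome (2.4, 2.5), no safety hypothesis is tested (6.1.3), and neither primary analysis changes. The section should be corrected, but the point does not threaten the study's main conclusions.

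**What to change.** - **Section 7.2:** apply the existing follow-up route, fax or e-mail once the therapist is informed, to SAEs during the 12-week intervention as well. Logs can still be collated after training ends.
- **Section 7, opening:** delete the condition that incidents be presumed training-related, and record relatedness as a separate item, adding a field to the telephone log if Appendix 8 lacks one.
- **Sections 7.1.2 and 7.2:** state one window for SAEs and use it in the definition and in the question asked at the call. The choice is the sponsor's; it should be explicit, and the recording window should not be widened as a side effect of the other edits.
- **Section 7.1.1:** state that any recorded event not meeting the SAE definition is an AE, whether or not treated.

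The cost is wording in section 7 and perhaps one log field, slightly more reporting work at the sites, and possibly higher event counts. Training, visits and sample size stay as they are.

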## **8. Use of the data and publication**

### **8.1. Reports**

#### **8.1.1. Interims report**

An interim report will be prepared for 25 patients included in the study and submitted to the project leader and all investigators of the participating trial centres.

#### **8.1.2. Final report**

A final report will be written up to three months after the end of the study and submitted to the project leader and all investigators of the participating trial centres.

### **8.2. Publication**

It is planned to present the results of the study in due course in scientific journals and/or at German and international congresses. For all publications, data protection will be ensured for all data of the persons concerned as well as for the data of the participating investigators.

Registration of the study in a public register in accordance with the recommendations of the International Committee of Medical Journal Editors (ICMJE) is also planned.

Publication or presentation of the results of this study, including publication or presentation by a single trial centre, is subject to prior acknowledgement, comment and approval by the sponsor. The number and order of authors for publications is/will be regulated in the cooperation agreement.

## **9. Changes of the study protocol**

For the purpose of ensuring largely comparable conditions in the interest of proper data evaluation, no changes to the agreed test conditions laid down in the test plan are envisaged. In exceptional cases, however, changes to the trial conditions are possible. These will only be made after mutual agreement between the sponsor, the sponsor representative and all signatories (authors) of this protocol. Any change to the study procedures provided for in the protocol must be made in writing, stating the reasons for the change, and must be signed by all authors of this protocol (amendment).

Subsequent amendments requiring approval according to § 10 para. 1 and 4 GCP-V will be submitted to the Ethics Committee for approval and will only be implemented after their approval. This does not apply to amendments that are necessary to avert immediate danger.

